### Sample size and power considerations

Among methadone-maintained smokers receiving a nicotine patch in a clinical trial, overall adherence over 90 days was 44.1 percent [12]. Assuming a 13-percent difference in adherence between the DOT and TAU groups as seen in weeks 2–12 of a methadone clinic-based antiretroviral DOT trial [30], the hypothesized adherence effect would be 57 percent in the mDOT arm and 44 percent in the TAU arm. We estimate sample sizes N per group required to detect this effect at a two-sided α = 0.05 as N per group = 11, 14, and 17 for intraclass correlation (ICC) = 0.1, 0.2, and 0.3, respectively.

Given that the efficacy of NRT and bupropion in methadone maintenance patients has been half of that observed in clinical trials of these medications in the general population [7,8,15], we estimate that abstinence rates at 12 weeks in the TAU varenicline arm would be 22 percent. We estimate that increased adherence would double the odds of cessation [13,17,18,46], and thus the abstinence rates at 12 weeks in the DOT arm would be 44 percent. We estimate sample sizes required to detect the hypothesized intervention effect (22% and 44% on a binary scale) at a two-sided alpha = 0.05 as N per group = 29, 33, 38 for within-subject ICC = 0.1, 0.2, and 0.3, respectively. Estimating an approximately 25 percent attrition rate at 12 weeks, we plan to recruit 100 participants.

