**Discussion:**

This trial will allow for rigorous evaluation of the efficacy of methadone clinic-based, directly observed varenicline for improving adherence and smoking cessation outcomes. This detailed description of trial methodology can serve as a template for the development of future DOT programs and can guide protocols for studies among opioid-dependent smokers receiving methadone treatment.

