This study also has limitations. Reasons for medication nonadherence are multifaceted. While a DOT strategy cannot address many potential adherence barriers, DOT interventions have demonstrated efficacy for improving adherence and clinical outcomes in TB and HIV. Generalizability to opioid-dependent persons outside of drug treatment may be limited. Nonetheless, over 200,000 people are enrolled in methadone programs in the US, over 80 percent of methadone maintenance patients smoke, and a significant number of methadone programs offer linked primary care services, including TB and HIV care. Furthermore, if proven effective, a DOT model could be used in other inpatient and outpatient substance abuse treatment settings. Finally, our modest sample size may not allow us to definitively evaluate moderating variables or to compare tobacco abstinence rates between the mDOT and TAU groups for smaller effect sizes. When we designed this study, there were no published studies on varenicline effects among methadone-maintained smokers. We have since completed a placebo-controlled trial of varenicline without DOT, in which 10.5 percent of varenicline-treated subjects were abstinent [57]. In another trial of varenicline, only 4 percent of methadone-maintained smokers achieved abstinence at the end of treatment [11].

Despite these potential limitations, we feel that our design will allow for a controlled evaluation of intervention effects, and our sample size will be adequate to assess adherence in both arms and to inform effect size estimation for future studies of smoking cessation interventions among methadone maintenance patients. Even if the cessation effect of this intervention is small, the potential health impact may be large, given the high prevalence of tobacco use and tobacco-related illness in substance abuse treatment patients.

This study has the potential to improve smoking cessation treatment outcomes and to inform the dissemination of smoking cessation services among substance abuse treatment patients. This, in turn, may reduce the disproportionate prevalence and associated disease burden of tobacco use in this difficult-to-treat group.

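### The abstinence sample size still rests on a 22% control rate that later trials reported in the same article put in doubt, and the limitations text does not say that the planned doubling itself is underpowered at those lower rates

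*Protocol article*

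**What the plan says.** The Sample size and power considerations section derives the control rate from nicotine replacement and bupropion, whose efficacy in methadone patients was taken to be half that in the general population: "we estimate that abstinence rates at 12 weeks in the TAU varenicline arm would be 22 percent". It continues "We estimate that increased adherence would double the odds of cessation", and "thus the abstinence rates at 12 weeks in the DOT arm would be 44 percent". The resulting requirement is "two-sided alpha = 0.05 as N per group = 29, 33, 38 for within-subject ICC = 0.1, 0.2, and 0.3, respectively". With about 25% attrition, 100 participants are to be recruited. The adherence calculation in the same section needs only 11 to 17 per group.

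The limitations paragraph of the main Discussion explains that no varenicline studies in this population had been published at the design stage. It then gives two later results: the team's own placebo-controlled trial without directly observed therapy, "in which 10.5 percent of varenicline-treated subjects were abstinent", and another varenicline trial in which "only 4 percent of methadone-maintained smokers achieved abstinence at the end of treatment". The same paragraph concedes that the modest sample may not allow abstinence to be compared for smaller effects. The next paragraph calls the sample adequate for adherence and for informing effect sizes in future studies.

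The Discussion part of the abstract is less guarded: "This trial will allow for rigorous evaluation of the efficacy", and it names smoking cessation outcomes as well as adherence.

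**The concern.** The planning rate is 22/10.5 = 2.1 times one later figure and 22/4 = 5.5 times the other. Sample size depends on the pair of rates, so a reader needs to know whether 29 to 38 per group still means anything if the control arm behaves as those trials suggest. The caveat about smaller effects reads as covering effects below the hypothesised doubling. It does not tell the reader that the doubling itself may be out of reach.

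Abstinence is the primary tobacco use outcome, and the Tobacco use analysis section tests a directional hypothesis on it. If power is low, a non-significant result is likely even when mDOT works, and it could be misread as evidence that mDOT does not help people quit.

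**Working it through.** **Inputs.** From the sample size section: 22% and 44%, two-sided alpha 0.05, ICC 0.1/0.2/0.3, 25% attrition, 100 recruited. From Randomization: 1:1 allocation. From the Discussion: 10.5% and 4%. Power and the number of repeated measures are not stated. I assume 80% and m = 3.

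**Reproducing the stated sizes.** For one time point, with p̄ = (p1 + p2)/2,

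n = [1.96√(2p̄(1−p̄)) + 0.842√(p1(1−p1) + p2(1−p2))]² / (p2−p1)²

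For 22% v 44%, p̄ = 0.33 and n = (1.303 + 0.544)²/0.0484 = 70.5. Multiplying by [1 + (m−1)ICC]/m with m = 3 gives 28.2, 32.9 and 37.6, so 29, 33 and 38. This matches exactly. With m = 4 at 80% power the formula gives 23, 29 and 34, which does not match. Some other variants come within a unit or two (for example 85% power with m = 4: 27, 33, 39), so the inferred settings are plausible but not certain.

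**Link to 100.** 38/0.75 = 50.7, or 51 per group against 50 planned. Evaluable at 12 weeks: 100 × 0.75/2 = 37.5 per arm.

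**Power at other rates.** With n_eff = N × 3/(1 + 2·ICC),

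power = Φ{[(p2−p1)√n_eff − 1.96√(2p̄(1−p̄))] / √(p1(1−p1) + p2(1−p2))}

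Example, 10.5% v 21%, N = 37.5, ICC 0.3: n_eff = 70.3; (0.881 − 1.010)/0.510 = −0.25; power 40%.

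| Control | mDOT | Effect carried over | N per group at 80% power, ICC 0.1/0.2/0.3 | Power, 37.5 per arm, ICC 0.1 to 0.3 | Power, 50 per arm, ICC 0.1 to 0.3 |
|---|---|---|---|---|---|
| 22% | 44% | as planned | 29/33/38 | 90-80% | 96-90% |
| 10.5% | 21% | rate doubled | 76/88/101 | 50-40% | 63-50% |
| 10.5% | 19.0% | odds doubled | 109/127/145 | 37-29% | 47-37% |
| 10.5% | 24.6% | odds ratio 2.79 | 46/53/61 | 72-60% | 84-72% |
| 10.5% | 32.5% | +22 points | 22/25/29 | 96-90% | 99-96% |
| 4% | 8% | rate doubled | 221/258/295 | 21-17% | 26-21% |
| 4% | 7.7% | odds doubled | 254/296/338 | 19-15% | 24-19% |
| 4% | 10.4% | odds ratio 2.79 | 102/119/136 | 40-31% | 50-40% |
| 4% | 26% | +22 points | 17/19/22 | 99-96% | over 99% |

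The odds ratio of 2.79 is the one implied by 22% v 44%: (0.44/0.56)/(0.22/0.78). In the 4% rows the normal approximation is rough, since 0.04 × 37.5 = 1.5 expected abstainers in the control arm.

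**Smallest detectable mDOT rate at 80% power.** Setting the power formula to 0.80 and solving for p2 with 37.5 per arm gives 26-29% from a 10.5% control rate and 16-19% from 4%.

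**Odds against rate.** Doubling the odds from 22%: 2 × 0.22/0.78 = 0.564, and 0.564/1.564 = 36.1%. For 22% v 36.1% the single-visit size is 162.3, and × [1 + 2·ICC]/3 gives 65, 76 and 87 per group, above the 50 planned. Power is 57-45% with 37.5 per arm and 69-57% with 50.

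**The case against.** Much of the defence stands.

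- A reader might infer that the two sections contradict each other. They do not. The Discussion says that the lower rates arrived after the design, and it reports them beside a caveat. This is an outdated assumption, partly disclosed.
- A reader might infer that the stated sizes are wrong, or that a lower control rate alone destroys power. Neither follows. The sizes reproduce for 22% v 44%, and a constant 22-point gain would need fewer participants. The loss arises when a relative effect is carried over. That is the natural reading, because the section argues from doubling. Keeping 22 points would mean an odds ratio of about 4.1 from 10.5%, or 8.4 from 4%, and the article offers no support for either.
- The trial is called a pilot, its primary outcome is adherence, and the Discussion already points towards estimation for cessation. This limits the severity, but the abstract does not carry the same restraint.
- The later rates may not transfer. The 10.5% has no stated time point, the 4% trial is not described as self-administered, and neither figure comes with an abstinence definition. This is a reason to show a range, not to substitute one rate.
- Using 37.5 per arm may be pessimistic, because a mixed model can use earlier visits from people lost by week 12. The 50-per-arm column covers this. Doubling the rate from 10.5% still reaches at most 63%.

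**Conclusion.** The point holds as an assumption overtaken by later data and only partly disclosed. At the later rates, a doubled abstinence rate has 40-63% power from 10.5% and 17-26% from 4%. Keeping the planned odds ratio of 2.79 gives 60-84% and 31-50%. Only an unchanged 22-point gain keeps power at about 89% or more. These figures rest on the inferred 80% power and three visits, ICC 0.1 to 0.3, 37.5 to 50 evaluable per arm, and the later rates being relevant to the self-administered arm.

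The odds slip needs no outside data: the stated basis, doubled odds, leads to 36.1%, while the calculation uses 44%.

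It would go too far to say that a null abstinence result is the expected outcome in every case. In the more favourable cases power is above one half, so such a result is likely rather than certain. What the documents do support is that the caveat is too narrow and that the abstract promises more on cessation than the Discussion sustains.

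**What to change.** Keep 100 participants.

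1. In Sample size and power considerations, restate power or the smallest detectable mDOT rate at control rates of 4%, 10.5% and 22%. State the effect scale, the assumed power, the number of visits and the evaluable number (37.5 to 50 per arm).
2. Reconcile the doubled odds with the 44%: either give 36.1% with its sample size, or describe and justify the effect as a doubled rate.
3. Describe the abstinence comparison as estimation, reporting the difference with a 95% confidence interval. This fits what the Discussion already says about informing future studies.
4. Limit the abstract's claim of a rigorous efficacy evaluation to adherence.

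The cost is wording and a short table. No participants, visits or measurements are added, but the stated power for abstinence becomes less favourable.

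### The planned 44% abstinence in the mDOT arm is a doubled rate, not doubled odds (36.1%), and 100 participants are underpowered for an odds ratio of 2

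*Protocol article*

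**What the plan says.** Under Sample size and power considerations, the article sets the control rate: "we estimate that abstinence rates at 12 weeks in the TAU varenicline arm would be 22 percent". It then gives the expected effect in words and draws the mDOT rate from it: better adherence "would double the odds of cessation [13,17,18,46], and thus the abstinence rates at 12 weeks in the DOT arm would be 44 percent". These two rates, 22% and 44%, go into the abstinence sample size, which is given "at a two-sided alpha = 0.05 as N per group = 29, 33, 38 for within-subject ICC = 0.1, 0.2, and 0.3, respectively". Allowing for about 25% attrition at 12 weeks, the article plans to recruit 100. It gives no power for this calculation and does not say how many repeated measures it assumes.

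The primary outcome is pill-count adherence (Adherence measures), which the same section sizes at 11, 14 and 17 per group. CO-verified 7-day abstinence is the primary tobacco use outcome (Tobacco use measures). It is to be compared across all follow-up visits with mixed-effects models (Tobacco use).

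**The concern.** The text presents 44% as the consequence of doubled odds, but at a base rate of 22% doubling the odds and doubling the rate are far apart. The step widens the planned difference from about 14 to 22 percentage points, and it sits in the calculation that produces the recruitment target. A reader would take 100 participants to be enough for an odds ratio of 2. If they are not, a non-significant abstinence result could be read as evidence against an effect that the trial had limited power to show.

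**Working it through.** **Inputs from the article.** Control rate 22%; effect in words, odds ratio 2; rate used for mDOT, 44%; two-sided alpha 0.05; ICC 0.1, 0.2, 0.3; 1:1 allocation; 25% attrition; 100 recruited, so 50 × 0.75 = 37.5 per group at week 12.

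**Assumptions.** Power of 80% and m = 3 measures per participant, back-solved as shown in step 2. Because Table 1 lists smoking endpoints at weeks 3, 6, 9, 12 and 24, m = 4 (treatment period) and m = 5 (with week 24) are shown too.

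**1. From odds to rate**
- Odds at 22%: 0.22/0.78 = 0.282. Doubled: 0.564.
- Rate: 0.564/1.564 = 36.1%.
- Odds ratio for 22% to 44%: (0.44/0.56)/(0.22/0.78) = 2.79.

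**2. Reproducing the printed sample size**

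For one measurement, with p̄ the mean of the two rates:

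n = [1.96·√(2p̄(1−p̄)) + 0.842·√(p₁(1−p₁) + p₂(1−p₂))]² / (p₂−p₁)²

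For 22% versus 44% this gives n = 70.5. Multiplying by [1+(m−1)·ICC]/m with m = 3 gives 28.2, 32.9 and 37.6, which round up to the printed 29, 33 and 38. Two-sided alternatives were tried with power of 80–95%, one to eight measures and several variance forms. Only 80% power with three measures came within 2 of all three figures.

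Attrition: 38/0.75 = 50.7, or 51 per group, close to 100 in total. The recruitment target therefore follows from the abstinence calculation.

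**3. The same formula with doubled odds**

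For 22% versus 36.1%, n = 162.3 for one measurement. With m = 3:

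| ICC | Printed N per group (22% vs 44%) | N per group (22% vs 36.1%) | Total after 25% attrition |
|---|---|---|---|
| 0.1 | 29 | 64.9 → 65 | 2 × 87 = 174 |
| 0.2 | 33 | 75.7 → 76 | 2 × 102 = 204 |
| 0.3 | 38 | 86.6 → 87 | 2 × 116 = 232 |

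Rounding the single-measurement n up to 163 first gives 66, 77 and 87.

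**4. Power for an odds ratio of 2 with 100 recruited**

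Effective n per group = n·m/[1+(m−1)·ICC]. For n = 37.5, m = 3 and ICC 0.1 this is 112.5/1.2 = 93.75, which gives power of 57%.

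| Measures | 37.5 per group, ICC 0.1 / 0.2 / 0.3 | 50 per group (no attrition), ICC 0.1 / 0.2 / 0.3 |
|---|---|---|
| 3 | 57% / 50% / 45% | 69% / 62% / 57% |
| 4 | 66% / 57% / 50% | 78% / 69% / 62% |
| 5 | 72% / 61% / 53% | 84% / 74% / 65% |

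For comparison, 22% versus 44% at 37.5 per group and m = 3 has power of 90%, 85% and 80%.

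**The case against.** **The rates used are printed, and N is right for them.** This stands. A reader might infer that the sample-size arithmetic itself is wrong; it is not. The fault lies in the step that justifies 44%. If a doubled rate was meant, one word is wrong and N holds, but the supporting evidence would then have to be for a rate ratio of 2. The cited sources are not at hand, so the article alone cannot settle which was meant.

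**The trial is a pilot with adherence as its primary outcome.** This also stands and limits the damage. The adherence sample size does not use the abstinence rates, so a reading that the error undermines the primary outcome is not supported. Abstinence is still the primary tobacco use outcome, has a directional hypothesis, and sets the recruitment target.

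**The Discussion already admits limited power.** It concedes that the sample may be too small to compare abstinence for smaller effects, and presents the trial as informing effect sizes for later studies. That softens the consequence. It does not tell the reader that the doubled odds used to justify 44% are themselves one of those smaller effects.

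**The low rates seen elsewhere.** A reader might count it as a further error that 22% was kept although the Discussion reports "We have since completed a placebo-controlled trial of varenicline without DOT, in which 10.5 percent of varenicline-treated subjects were abstinent" and, from another trial, that "only 4 percent of methadone-maintained smokers achieved abstinence at the end of treatment". The documents do not support that. The article says no such data had been published at the design stage, and it discloses both rates as a limitation.

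**The size rests on unstated inputs.** This is true. A flat claim of even odds or worse would hold only for some of the scenarios above, which is why a range is given.

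**Conclusion.** The sentence is wrong as written: doubled odds from 22% give 36.1%, and 44% corresponds to an odds ratio of about 2.8. That part needs no assumption, and nothing elsewhere in the article corrects it.

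The trial is underpowered for an odds ratio of 2, which is weaker than saying it cannot detect one. At the planned attrition, power is 45–72% across three to five measures and the stated ICCs, and no case tried reaches 80%. Mixed models can use the early visits of participants who later leave, so the position may lie between the two columns of the power table. Even with no attrition, only five measures at ICC 0.1 passes 80% (84%). The required 65, 76 and 87 per group depend on the assumed 80% power and three measures.

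**What to change.** In Sample size and power considerations, do one of the following.

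- **Keep the doubled odds.** Replace 44% with 36%. Restate the required N (about 65, 76 and 87 per group at 80% power with three measures) and the power that 100 participants give. State the power and the number of measures assumed.
- **Keep 44%.** Say that the planned effect is a doubling of the abstinence rate, an odds ratio of about 2.8, and remove the doubled-odds justification.

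In neither case should the text say that 100 participants are justified by adherence. That outcome needs 11–17 per group; at the upper figure, 17/0.75 = 22.7, or 23 per group, which is 46 in total.

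Power at the two lower control rates in the Discussion is an optional addition. With three measures and 37.5 per group, doubled odds from 10.5% (to 19.0%) have power of about 29–37%, and from 4% (to 7.7%) about 15–19%.

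The cost is wording only. Under the first option a stated figure becomes less favourable; neither option requires more participants or a change of design.

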### Dissemination policy

We will disseminate study findings at national scientific meetings and in published manuscripts. On request, we will also share study protocols and de-identified study data with investigators for research purposes. No study participants will be individually identified in any published or shared data.

### Study design considerations

#### Optimizing pill count adherence measurement

For mDOT arm subjects, varenicline dosing will be evaluated by directly counting unconsumed varenicline pills remaining behind the methadone window, as well as those returned to nurses in pill boxes. Unobserved doses in unreturned pill boxes will be counted as nonadherence. Each day, nurses also will complete a pre-printed calendar documenting whether doses were dispensed, refused, or if the subject missed clinic.

Since a 4-week supply of 1 mg varenicline tablets can be dispensed in bottles (containing 56 tablets) or in four weekly blister packs (each containing 14 tablets), TAU group subjects will be asked to bring in the full month’s supply of medication to each study visit for pill counting. For TAU arm subjects, research assistants will count pills remaining in varenicline bottles or blister packs at weeks 1, 2, 3, 6, 9, and 12. Given that TAU subjects obtain a 4-week supply of medication at a time from community pharmacies, and that pill-count adherence would be challenging to interpret if no pills were remaining, we designed the research visit schedule to assess pill count adherence separately from the every-4-week medication dispensing intervals. To ensure pill count completion, TAU group subjects will be given partial reimbursement ($5-$10 dollars per visit) for completion of research assessments and $5 for completion of pill counts at each follow-up visit during the intervention period.

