### Interventions

Subjects will receive varenicline for 12 weeks, using standard dosing: 0.5 mg once daily for 3 days, then 0.5 mg twice daily for 4 days, followed by 1 mg twice daily for 11 weeks. Subjects will be randomly assigned to receive varenicline via: 1) treatment as usual (TAU) or 2) modified directly observed therapy (mDOT). Most subjects will have public insurance that should cover the cost of varenicline; for those who do not, varenicline will be purchased from a local pharmacy using research funds.

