### Varenicline adherence

We hypothesize that adherence in the mDOT arm will be higher than in the TAU arm throughout the intervention period. We will apply a mixed effects linear model to test the significance of the mDOT effect on the repeatedly measured pill count adherence outcome at weeks 1, 2, 3, 6, 9, and 12. This model accounts for within-subject longitudinal outcome correlation by taking the subject-level intercept as random, and it is robust in the context of missing data. The model will also include variables not equally distributed between the study arms at baseline, as well as psychiatric symptoms and substance abuse. All analyses will use an intent-to-treat approach.

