#### Addressing varenicline risk potential

Case reports of behavior change, agitation, depression, and suicidality among patients taking varenicline led to an FDA boxed warning in 2009 [47]. Despite a growing body of research demonstrating the safety of varenicline among patients with mental illness and substance use disorders [48-56], we will take multiple precautions to address varenicline’s psychiatric risk potential.

Prior to enrollment, information regarding potential psychiatric risks will be discussed with subjects during the informed consent process. During screening, a physician will assess potential subjects for current psychiatric illness or suicidal ideation using structured instruments. Individuals with psychiatric symptoms not receiving psychiatric care will be referred to a mental health center.

Subjects will be assessed for incident psychiatric symptoms throughout the intervention period. At brief visits (weeks 1 and 2), and weeks 3, 6, 9 and 12, the interviewer will ask open-ended questions about symptoms that have emerged or increased in intensity since the prior visit. At week 3, 6, 9, and 12 follow-up visits, psychiatric symptoms will be assessed via structured instruments. Prior to concluding the research visit, the research assistant will review flags programmed into the computerized survey record for symptoms consistent with incident major depressive or manic episode, psychotic disorder, or suicidal ideation and will refer subjects to outpatient or emergency treatment according to detailed study protocols.

If subjects meet criteria for current major depressive or manic episode, psychotic disorder, or suicidal ideation with plan or intent, varenicline will be discontinued. To facilitate medication discontinuation among TAU group subjects who fill varenicline prescriptions at community pharmacies of their choosing, prescriptions will not be given directly to study subjects; rather, the study physician will call in all prescriptions and track the pharmacies used. If DOT group subjects meet criteria for medication discontinuation, the study physician will notify the study pharmacy and the methadone clinic nurses.

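### The week-12 pill count in the TAU arm falls where a zero is expected, so the visit schedule misses its own aim at the last of the six primary-outcome measurements

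*Protocol article*

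**What the plan says.** The primary outcome is pill-count adherence, expressed as a percentage of the target dose over the 12-week course (Protocol article, *Adherence measures*). The primary mixed model uses the "repeatedly measured pill count adherence outcome at weeks 1, 2, 3, 6, 9, and 12" (*Varenicline adherence*).

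The rest comes mainly from *Optimizing pill count adherence measurement*:

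- **Supply.** The passage on scheduling begins "Given that TAU subjects obtain a 4-week supply of medication at a time from community pharmacies". A 4-week supply of 1 mg tablets "can be dispensed in bottles (containing 56 tablets) or in four weekly blister packs (each containing 14 tablets" each).
- **Problem recognised.** The authors note that "pill-count adherence would be challenging to interpret if no pills were remaining".
- **Answer given.** For that reason, "we designed the research visit schedule to assess pill count adherence separately from the every-4-week medication dispensing intervals".
- **TAU counts.** In the TAU arm, "research assistants will count pills remaining in varenicline bottles or blister packs at weeks 1, 2, 3, 6, 9, and 12".
- **mDOT rule.** Home doses whose box never comes back are scored as not taken. No matching rule is given for TAU tablets that are not presented.

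Table 1 starts treatment at baseline and marks week 12 as the end of treatment. Under *Addressing varenicline risk potential*, "the study physician will call in all prescriptions and track the pharmacies used". The stated purpose there is to make stopping the drug easier; the article does not link this tracking to the adherence measure.

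**The concern.** The schedule is presented as the safeguard against uninformative zero counts in TAU. Week 12 is three full 4-week supplies after baseline, so a participant who fills on time and takes every tablet arrives with none. That is the situation the authors say they wanted to avoid.

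At any other visit an empty bottle is a warning, because an adherent participant should still hold tablets. At week 12 an empty bottle is what perfect adherence looks like, and also what losing or discarding the remaining tablets looks like.

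The ambiguity bears on the treatment comparison because missing tablets are handled by a stated rule in one arm only. Unreturned mDOT home doses count against adherence. If TAU tablets that are not presented count as taken, the comparison is tilted towards TAU and the estimated mDOT effect shrinks.

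**Working it through.** **Inputs**
- Dosing: "0.5 mg once daily for 3 days, then 0.5 mg twice daily for 4 days, followed by 1 mg twice daily for 11 weeks" (*Interventions*).
- TAU supply: 4 weeks per fill; counts at weeks 1, 2, 3, 6, 9 and 12 (*Optimizing pill count adherence measurement*).
- Assumptions: one tablet per dose, first fill at baseline, refills on time at weeks 4 and 8, and each fill matching the schedule.

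**1. The plan's own figure.** 2 tablets/day × 28 days = 56 = 4 × 14. The stated pack size is reproduced.

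**2. Target tablets.** 3 days × 1 + 81 days × 2 = 165. By supply: weeks 1–4, 3 × 1 + 25 × 2 = 53; weeks 5–8, 56; weeks 9–12, 56. Sum 53 + 56 + 56 = 165.

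**3. Tablets left under full adherence** = tablets dispensed to date − tablets scheduled to date.

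| Visit (week) | Dispensed | Scheduled | Left |
|---|---|---|---|
| 1 | 53 | 11 | 42 |
| 2 | 53 | 25 | 28 |
| 3 | 53 | 39 | 14 |
| 6 | 109 | 81 | 28 |
| 9 | 165 | 123 | 42 |
| 12 | 165 | 165 | 0 |

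Only week 12 lands at the end of a supply.

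**4. Share of the outcome.** Weeks 9–12 hold 21 days × 2 = 42 tablets; 42/165 = 25.5%. A participant with a correct week-9 count who then loses or discards all 42 has true adherence of 123/165 = 74.5%, with a final count that is compatible with 100%.

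**5. Possible bias.** Let p be the share of TAU participants whose week 9–12 tablets were not taken but are read as taken. The documents give no value for p, so a range is shown. The figures are upper limits, because they suppose that none of the 42 tablets was taken.
- Weighted by tablets: p × 42/165. For p = 10%, 20%, 30%: 2.5, 5.1, 7.6 points.
- Six visits weighted equally: p × 100/6. For the same p: 1.7, 3.3, 5.0 points.

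The planned difference is 13 points (57% against 44%, *Sample size and power considerations*).

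**6. Sensitivity to fill dates.** A third fill that is L days late, with full adherence from then on, leaves 2 × L tablets at week 12: 2, 14 or 28 tablets for 1, 7 or 14 days. The exact zero applies to on-schedule fillers.

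**The case against.** **Week 12 is not a dispensing date.** Fills fall at weeks 0, 4 and 8, and no count coincides with one, so the sentence can be defended literally. But the reason given for the schedule is to avoid counts with nothing left, and week 12 fails on that reason.

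**Loss and discarding limit every pill count.** This stands. It holds at other visits and in mDOT, where 8 of 14 weekly doses go home even on a six-day clinic schedule, and a returned empty box does not prove ingestion. What is particular to TAU at week 12 is that complete loss matches the expected count exactly, and no rule is stated for tablets that are not presented.

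**Stronger readings that a reader might infer:**
- *That the last nine weeks are compromised*, since the intervals ending at weeks 6, 9 and 12 hold 126 of 165 tablets (76%). This is not supported. Adherent participants should show 28 tablets at week 6 and 42 at week 9, so a zero there is unexpected and would flag a skipped fill.
- *That someone who never filled the third supply passes as adherent at week 12.* The week-9 visit, one week after that fill is due, should expose this, because TAU participants are asked to bring their whole current supply to each count.
- *That the plan scores a zero as taken.* No passage says so. The direction of bias is conditional on that scoring.
- *That fill dates and quantities are not collected.* The article does not say this, and a condensed article may leave such bookkeeping to the full protocol.

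**Conclusion.** The point holds for one of the six repeated measures. For TAU participants who fill on schedule, the week-12 count lacks the property the schedule is said to secure, and it enters the primary model. The affected interval is 42 of 165 target tablets (25%).

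The contradiction follows from the article's own dates and the on-time fill assumption. The size of any bias does not: it depends on an assumed misread share and on missing TAU tablets being read as taken. Under those assumptions TAU adherence is overstated and the mDOT effect diluted. The effect on overall TAU adherence runs from about 1.7 to 7.6 points across the range examined, depending on the share and the weighting. Those figures show why the scoring matters; they are not an estimate of what will occur. The correction is worth making because it concerns the primary outcome and is inexpensive.

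**What to change.** 1. Compute TAU tablets taken as tablets dispensed, with date and quantity confirmed by the pharmacies already tracked, minus tablets counted.
2. Credit a zero count at week 12 as taken only when the third fill is confirmed and the empty bottle or packs are shown. Treat a missing container as nonadherence, in line with the mDOT rule for unreturned boxes.
3. Repeat the primary mixed model without the week-12 measurement as a sensitivity analysis. This is needed because an empty container still cannot show that its tablets were swallowed rather than discarded.
4. Correct the sentence on visit timing to say that week 12 does not meet the stated aim.

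The cost is fill records for about 50 TAU participants (half of the 100 planned) and one extra model run. The visit schedule does not change. Moving the last count to week 11 is not recommended: it would leave the final 14 target tablets unmeasured, while the outcome is defined over the full 12 weeks.
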